### Limitations

Technical limitations have impeded the study of longitudinal changes in sleep microstructure during the index course of ECT. While battery-operated wireless wearable devices allow continuous long-term EEG recordings in the inpatient and outpatient settings, these devices are equipped with dry electrodes that may be more prone to artifacts due to poor skin adherence. Thus, advanced filtering techniques are required to identify and suppress artifacts from EEG signals to fulfill the promise of this technology for large-scale sleep investigations in patients with mental health disorders. Another limitation of this study includes the potential existence of nonlinear relationships between dependent and independent variables in our analyses as different ECT stimulation montages may have posed different effects on sleep and seizure markers. These nonlinear relationships might not be explained by linear mixed-effect models. In such cases, generalized mixed-effect models will be utilized for data analyses. Another potential limitation in our study lies in the use of different classes and dosages of anesthetic agents and muscle relaxants during ECT sessions which may increase variance in data. Finally, while QIDS-SR16 has been reported to be a reliable and valid scale for assessing the severity of depression, it may contribute to sample variability compared to clinician-rated scales on depression such as HAMD or MADRS.

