### Electroconvulsive therapy

Electroconvulsive therapy will be delivered using standard-of-care clinical protocols. Three stimulation electrode placements will be utilized: right unilateral (electrodes placed on the right temple and vertex of the head), bilateral (electrodes placed on the right and left temple), and bifrontal (both electrodes placed on the forehead, above the outer canthus of the eye).

Prior to ECT stimulation, general anesthesia will be induced. Commonly used regimens include etomidate 0.2 mg/kg, methohexital 1 mg/kg, or ketamine 1.5 mg/kg. The anesthetic regimen will be determined at the anesthesiologist’s discretion. Standard American Society of Anesthesiologists safety monitoring will occur throughout treatment.

The ECT stimulation will be delivered *via* routine clinical practice, using the Thymatron System IV. On the initial treatment (dose titration) session, ECT-naïve individuals typically receive right unilateral ECT titration at 5% charge, 0.3 ms pulse-width, 40 Hz frequency. While a seizure duration of 20–25 s has been accepted to be adequate by some, there are no firm data that support this position. Instead, seizure duration appears to not determine adequacy of response (88–93). Therefore, at our institution seizure duration is not used to determine adequacy of the treatment. Instead, a seizure duration of 10 s is defined as a reasonable minimal limit for determining the presence of an induced seizure. If an appropriate seizure is not obtained after this initial stimulation, then ECT charge will be increased in a protocolized fashion until a seizure of at least 10 s is obtained. Subsequent right unilateral treatments are then administered at a charge sixfold above seizure threshold.

If, based upon the clinical judgment of the ECT clinician, right unilateral ECT at sixfold seizure threshold does not improve depressive symptoms, participants may then transition to 100% right unilateral charge and if need be bilateral ECT at two-times seizure threshold. If during the course of ECT seizure duration becomes less than 10 s, then modifications, based on the exact clinical situation will be made by the ECT psychiatrist in how ECT is provided in order to increase duration to above 10 s.

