### Statistical analysis

Linear mixed-effects models will be constructed to account for missing data without the need for data imputation or deletion. Models will be generated in MATLAB. To characterize SWA over the course of ECT, linear mixed-effect models will be constructed using SWA as a dependent variable and treatment number as an independent variable. Similarly, to examine sleep spindle density changes, linear mixed-effects models will be generated that have sleep spindle density as a dependent variable and treatment number as an independent variable. Associations between CPC and sleep SWA or sleep spindles will be evaluated *via* respective linear mixed-effect models. For all aims, separate models will be constructed for responder and non-responder groups. QIDS-SR16 scores and ECT stimulation *parameters* will be entered as covariates for all analyses, as appropriate.

A total number of 25 participants will be targeted for recruitment in this study. Sample size calculations are based on the published data following conventions for statistical power analysis in the behavioral sciences (100) and our best guesses regarding effect size and SD. The main factor that we considered in estimating our required sample size was based on reported changes in SWA measure in major depression (98, 101, 102). We estimate a medium effect size and a partial η^2^ value of 0.1. Thus, we estimate sample sizes of 17 (power of 0.8, alpha of 0.05) based on a conservative assumption on the number of treatments (10 treatments) to account for missing a session or poor quality of EEG data. Participants may withdraw from the study at any time, and we will track reasons for patient attrition. Given that a previous study on a similar patient population cohort conducted at Barnes-Jewish Hospital and Washington University showed a 30% attrition rate (80), we expect to have at least 17 participants with interpretable data in the current study.

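### The fallback for nonlinear or placement-dependent courses is a generalized mixed model, which by itself provides neither a flexible course over treatments nor a placement-specific slope

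*Protocol article*

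**What the plan says.** Under Statistical analysis, Aim 1 is analysed so that "linear mixed-effect models will be constructed using SWA as a dependent variable and treatment number as an independent variable". Spindle density is handled in the same way, with separate models for responders and non-responders. On covariates, the section says: "QIDS-SR16 scores and ECT stimulation *parameters* will be entered as covariates for all analyses, as appropriate".

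Under Electroconvulsive therapy, "Three stimulation electrode placements will be utilized": right unilateral, bilateral and bifrontal. That section also describes how a participant may move from one placement to another during the course.

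Under Limitations, the article raises this possibility: "potential existence of nonlinear relationships between dependent and independent variables in our analyses as different ECT stimulation montages may have posed different effects". The outcomes it has in mind are the sleep measures and the ictal EEG measures. It continues: "These nonlinear relationships might not be explained by linear mixed-effect models". The remedy follows at once: "In such cases, generalized mixed-effect models will be utilized for data analyses". No link, outcome distribution, curved term for treatment number or placement-by-treatment-number term is named.

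**The concern.** The Limitations section states a rule for what to do if the linear model fails, and the tool it names does not match the failure it describes.

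Two problems are run together. Curvature means that the mean course over treatment number is not a straight line, for example an early rise that levels off. Effect modification means that the course differs by electrode placement, and each course may itself be perfectly straight. The first needs a curved term for treatment number. The second needs an interaction between placement and treatment number. Both fit inside an ordinary linear mixed model. Moving to a generalized model changes how the outcome is distributed around its mean and the scale on which the predictor acts. It adds neither term.

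The longitudinal course of SWA and spindle density is the primary objective. An analyst who detected curvature and did only what the sentence says could report a generalized model whose predictor is still linear in treatment number, believing the problem solved.

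**Working it through.** **The plan's own figure.** The article says "We estimate a medium effect size and a partial η^2^ value of 0.1" and arrives at 17 participants with 10 treatments, power 0.8 and alpha 0.05. With f = √(0.1/0.9) = 0.333 and a repeated-measures F test, the requirement is 16 (sphericity, zero correlation between measures) or 18 (noncentrality f²(n−1)(m−1)). So 17 is reproduced to within one. Attrition: 17/(1 − 0.30) = 24.3, rounded up to 25. The point does not depend on this figure; it shows only how few participants any extra term would rest on.

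**Check 1: curvature.** The documents give no expected shape, so the curves are assumptions.
- Mean course: y(t) = 1 + A(1 − e^(−t/τ)), t = 1,…,10, with τ = 1, 2 or 3 treatments. A runs from 0.2 to 1.0, a rise of 20% to 100% of baseline.
- Fits: noise-free least squares, R² = 1 − SS(residual)/SS(about the mean).
- The spline is restricted cubic with knots at the 10th, 50th and 90th percentiles of t (1.9, 5.5, 9.1).

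| τ | straight line | log link | quadratic | 3-knot spline |
|---|---|---|---|---|
| 1 | 0.51 | 0.50–0.51 | 0.85 | 0.83 |
| 2 | 0.75 | 0.72–0.74 | 0.97 | 0.96 |
| 3 | 0.86 | 0.83–0.85 | 0.99 | 0.99 |

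The log-link range covers A = 1.0 down to 0.2. The other columns do not depend on A.

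What a straight line hides, at τ = 2 in units of A:
- The true rise from treatment 1 to 2 is e^(−0.5) − e^(−1) = 0.607 − 0.368 = 0.239.
- The true rise from treatment 9 to 10 is e^(−4.5) − e^(−5) = 0.0111 − 0.0067 = 0.004.
- The fitted line gives 0.056 at every step. The rate of change is therefore too low early and too high late.
- The fitted level lies 0.20 above the truth at treatment 1, 0.10 below it at treatment 5 and 0.11 above it at treatment 10.

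Other assumed shapes:
- A symmetric inverted U peaking mid-course: R² is 0.00 under identity, log and inverse links, and 0.99 with the spline.
- An exponential rise, e^(0.06t): 1.000 with a log link, but already 0.994 with a straight line.

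**Check 2: placement-dependent slope.** Assume two placements with equal data, y = 1 + 0.06t in A and y = 1 in B. The true change from treatment 1 to 10 is 9 × 0.06 = 0.54 in A and 0 in B. Estimated changes (A / B):

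| predictor | identity | log | inverse |
|---|---|---|---|
| treatment number | 0.27 / 0.27 | 0.27 / 0.27 | 0.27 / 0.27 |
| + placement main effect | 0.27 / 0.27 | 0.35 / 0.26 | 0.41 / 0.23 |
| + placement × treatment number | 0.54 / 0.00 | 0.54 / 0.00 | 0.53 / 0.00 |

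The interaction separates the two courses, and it does so exactly in the ordinary linear model. Changing the link without it does not.

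**Check 3: is a quadratic enough?** On the saturating curves the fitted quadratic turns down at treatment 7.1, 7.8 and 8.7 (τ = 1, 2, 3), a decline that is not there. From its highest fitted treatment to treatment 10 it falls by 0.08, 0.06 and 0.02 of A. The spline falls by 0.06, 0.03 and 0. The spline is the better choice, though it too shows a slight false dip for the fastest plateau.

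**The case against.** The case on the other side has real force in four places.

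- **A non-identity link does bend the mean.** A reader might infer that the fallback can never represent a curved course. It can represent one monotone shape, set by the link, as the exponential example shows. This stands; the point is limited to shapes the link does not match.
- **Naming a model class does not exclude further terms.** Splines or interactions can be put into a generalized mixed model, and an article may leave such detail to the full analysis plan. This stands in part. The complaint is not that detail is absent. The text offers the change of model class as the answer to nonlinearity, and that change is not what would resolve it.
- **Placement may already be adjusted for.** A reader might infer that placement is ignored. The Statistical analysis section enters stimulation parameters as covariates, and the Introduction uses electrode placement as an example of an ECT parameter. Level differences between placements are thus plausibly covered, and only different slopes are left open.
- **It is a contingency.** The models for the aims are set out under Statistical analysis, and the sentence does not replace them. For a steady plateau, a linear trend still has the right sign. This stands and lowers the severity.

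One might also infer that a log link would make matters clearly worse. With a positive baseline, as SWA power must have, the difference from a straight line is at most 0.03 in R² in the cases above, so that is not claimed.

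**Conclusion.** The point holds as a minor one. The Limitations section merges curvature over treatment number with effect modification by electrode placement, and commits to a model class that by itself resolves neither beyond one link-fixed monotone curve. Under the assumed saturating courses, a straight line explains 51–86% of the trend variance, a log link 50–85%, and a three-knot spline 83–99%. Under an assumed symmetric rise and fall, no change of link helps. When slopes differ by placement, the interaction is what recovers them.

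These sizes rest on assumed, noise-free curves and show direction and order of magnitude only. The documents do not say that the course will plateau, turn, or differ by placement. They also do not support the stronger reading that the planned primary models are wrong or that placement goes wholly unadjusted.

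**What to change.** Replace the sentence on generalized models in Limitations with:

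> Departure from linearity will be assessed by adding a restricted cubic spline (3 knots) for treatment number to the same linear mixed model. As a sensitivity analysis, electrode placement as a time-varying factor and its interaction with treatment number will be added where the data allow. Generalized mixed models will be used only if the outcome distribution requires it.

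The cost is wording plus parameters: one for curvature, and up to four for three placements (two main effects and two interactions). With about 17 evaluable participants split into responder and non-responder models, these would be imprecise. At the Introduction's upper response rate of 80%, the non-responder model would rest on 17 × 0.2 = 3.4, so three or four people. For that reason the interaction should stay a sensitivity analysis, and a small late dip in a fitted spline should not be read as a real decline.

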## Conclusion

The CET-REM study will probe longitudinal changes in sleep microstructure and seizure markers over the index course of ECT. Wireless wearable devices will be utilized for at-home unattended collection of sleep EEG to provide measures of sleep slow waves and sleep spindles. ECT-induced seizure markers will be assessed using high-density EEG recordings. Overall, the results from this study will elucidate underlying mechanisms and markers for responsiveness to ECT.

## Ethics statement

The Washington University Human Research Protection Office (WU HRPO) reviewed and approved this study involving human participants. Informed consent will be obtained for all participants prior to the conduct of any study procedures. Written informed consent was obtained from the individual(s) for the publication of any identifiable images or data included in this article.

## Abbreviations

AASM: American Academy of Sleep Medicine
BDNF: brain-derived neurotrophic factor
CPC: central-positive complexes
CET-REM: Correlating ECT Response to EEG Markers
DSR: delta sleep ratio
ECT: electroconvulsive therapy
EEG: electroencephalography
EDF: European Data Format
MDD: major depressive disorder
NREM: non-rapid eye movement
N1: NREM sleep stage 1
N2: NREM sleep stage 2
N3: NREM sleep stage 3
PSG: polysomnography
PSQI: Pittsburgh Sleep Quality Index
QIDS-SR16: Quick Inventory of Depressive Symptomatology-16 Self Report
SWA: slow wave activity
REM: rapid eye movement.
